### Methods for additional analyses (e.g., subgroup analyses) {20b}

#### Missing and deviating values

Subgroup analyses will be performed for both primary and secondary outcomes to determine the impact of key patient characteristics (e.g., age, comorbidities, drug use) and hematoma characteristics (e.g., size of hematoma) on the effect of treatment. Heterogeneity across patient and hematoma characteristics will be tested using logistic regression models for categorical outcomes and a linear regression model for continuous outcomes including the cross-product between intervention and subgroup characteristic as an explanatory variable.

#### Data transformation and calculated variables

Data transformation or calculation of variables is not applicable for primary or secondary outcomes. In order to utilize parametric tests, some continuous baseline variables may be subjected to transformation (e.g., log transformation or categorization) in order to assure normal distribution.

#### Adjustment of significance levels and confidence intervals

The study includes one primary outcome and five secondary outcomes. Threshold for statistical significance is set at *P* < 0.05 for the primary outcome. For secondary outcomes, correction for multiple testing will be performed using a significance level of *p* < 0.01.

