### Objectives {7}

Research hypothesis: Embolization of the middle meningeal artery (eMMA) reduces the reoperation frequency of chronic subdural hematoma compared to standard neurosurgical treatment.

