#### Secondary outcome measures:

I.Difference in neurologic disability, assessed by modified Rankin Scale (mRS), between groups at 3 and 12 monthsII.Difference in quality of life, assessed by EuroQoL 5D (EQ-5D) between groups at 3 and 12 monthsIII.Difference in residual hematoma volume (mL) between groups, assessed by NCCT of the head at 3 months post treatmentIV.Technical success rate of endovascular treatment (percentage of interventions), defined as post procedurally no visualization of antegrade flow in branches of the MMA distal to non-target arterial branches, i.e., arteries to the orbit or cranial nerves, on final angiogramV.All complication rates; number and severity of adverse and serious adverse events between groups.VI.Composite endpoint: difference in death or reoperation frequency within 3 and 12 months after treatment between groups

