#### Secondary variable analyses

Binary secondary outcomes (i.e., technical success rate, all complications rate, and composite outcome of death and re-operation within 3 months) will be analyzed using logistic regression models (as described for the primary outcome). Kaplan–Meier time-to-event analysis with follow-up time as the time scale will also be used to assess the impact of intervention on the composite outcome of death and re-operation with differences between survival curves assessed using the likelihood ratio test. Ordinal secondary outcomes (i.e., mRS and EQ5D) will be assessed at 3 and 12 months after treatment. To assess the effect of intervention at each time point, ordinal logistic regression models will be used. For the continuous secondary outcome (i.e., hematoma volume), a generalized linear model will be used. All analyses will account for enrolment center and baseline characteristics unevenly distributed between study arms when applicable.

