#### Data Safety Monitoring Board

The Data Safety Monitoring Board (DSMB) comprises at least 3 non-Investigator clinicians with expertise in interventional neuroradiology/neurosurgery that will review all adverse events occurring in the study according to the DSMB Charter. The DSMB will meet and review all clinical events continuously.

Any event meeting the definition of serious adverse event (SAE) must be adjudicated by the DSMB. The DSMB will also be provided with listings of all events and may choose to adjudicate events that are not serious in nature. Members may discuss any event with the investigator who was involved with the subject in question. The DSMB will use the same rating scale for relatedness. The DSMB adjudicated adverse events will be used in the analysis of the primary safety endpoint; DSMB will review and adjudicate the Medical Monitor’s categorization of event type and severity using the rating system previously referenced.

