## Discussion

The hypothesis of this trial is that endovascular treatment alone is safe and effective with a reduced reoperation rate compared to surgical evacuation in cSDH patients with clinical indication for surgical treatment.

The rationale for the trial design is the encouraging results with reduced reoperation rate for patients treated by endovascular embolization alone, where the reoperation rates are similar to those seen for endovascular treatment adjuvant to surgical evacuation. However, when routinely using endovascular treatment as an adjunctive, the increased complication rate by having two separate procedures may potentially outweigh any benefit of the combined treatments.

A minimally invasive treatment with reduced recurrence risk and comparable complication rates has however the potential for paradigm shift in the treatment of cSDH. Not within the scope of this trial, but eMMA has also been associated with a reduction in healthcare costs, the primary driver being fewer treatments needed [20]. A drawback of the endovascular treatment is that resolution of the hematoma is slower than prompt neurosurgical evacuation. Limited data on timing of clinical improvement with upfront eMMA is currently available. In our experience, a delay of clinical and radiological improvement of 5–10 days and 4–6 weeks respectively can be expected.

Internationally, treatment strategies for bilateral cSDH varies significantly, and reoperation rates for this group seem to be somewhat higher than unilateral cSDH, either by ipsilateral recurrence or opportunistic expansion of the unoperated side [21]. For bilateral cSDH randomized to neurosurgery and unilaterally evacuated at index procedure, additional analysis including subsequent operative treatment on the contralateral side will be performed.

When designing this trial, we have striven to follow clinical routine care as much as possible to facilitate transferal into clinical routine care, should the results be positive.

The trial is academically driven and locally funded by the collaborating efforts of the Neurosurgery and Interventional Neuroradiology departments at Skåne University Hospital. Sponsor is Region Skåne, the publicly funded healthcare provider for the south region of Sweden.

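### Complications are judged at the multiplicity-corrected p<0.01, which makes a real excess harder to declare in a trial whose stated hypothesis includes safety

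*Protocol article*

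**What the plan says.** The formal research hypothesis (Objectives {7}) concerns reoperation only: "Embolization of the middle meningeal artery (eMMA) reduces the reoperation frequency of chronic subdural hematoma compared to standard neurosurgical treatment". The Discussion states it more widely: "The hypothesis of this trial is that endovascular treatment alone is safe and effective with a reduced reoperation rate compared to surgical evacuation". A separate sentence there says what could change practice: "A minimally invasive treatment with reduced recurrence risk and comparable complication rates has however the potential for paradigm shift".

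Complications are item V under Secondary outcome measures: "All complication rates; number and severity of adverse and serious adverse events between groups". Secondary variable analyses covers how they are analysed: "Binary secondary outcomes (i.e., technical success rate, all complications rate, and composite outcome of death and re-operation within 3 months) will be analyzed using logistic". The regression model is the one used for the primary outcome, which Primary variable analyses describes as giving odds ratios with 95% confidence intervals. All tests are two-sided.

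Adjustment of significance levels and confidence intervals keeps 0.05 for the single primary outcome and then says: "For secondary outcomes, correction for multiple testing will be performed using a significance level of *p* < 0.01". Safety outcomes are not exempted.

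The Data Safety Monitoring Board section adds: "The DSMB adjudicated adverse events will be used in the analysis of the primary safety endpoint". The article defines no such endpoint.

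**The concern.** A stricter threshold for secondary outcomes limits false positive claims. That is the right direction when a positive result favours the new treatment. For complications the costly error is the opposite one: failing to declare an excess that exists. Moving from 0.05 to 0.01 makes that error more likely.

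The trial is sized for reoperation, not for safety. If the primary comparison succeeds and the complication test is labelled not significant, the two together invite the reading that embolization is superior and about as safe as surgery. The article foresees that a favourable result could lead to embolization replacing open surgery in old and fragile patients, so the safety half of that reading matters.

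**Working it through.** **Inputs from the protocol.** 144 patients per arm; primary rates 17% v 6.5%; two-sided likelihood ratio test at 0.05 with 80% power (Sample size {14}); 0.01 for secondary outcomes. **Assumed:** all complication rates, because the protocol gives none.

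**1. Reproduce the stated sample size.** With mean rate 0.1175, the likelihood ratio divergence per patient pair is

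d = 2[0.17 ln(0.17/0.1175) + 0.83 ln(0.83/0.8825) + 0.065 ln(0.065/0.1175) + 0.935 ln(0.935/0.8825)] = 0.0549.

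n = (1.960 + 0.842)²/d = 143.06, rounded up to 144 per arm, as stated. Enumerating both binomials at 144 per arm gives 80.9% power, so the method below matches the protocol's own.

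**2. Power to declare an excess of complications.** Same enumeration and test, counting rejections in the direction of harm from embolization. Critical values are 3.841 (0.05) and 6.635 (0.01).

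| Assumed rates, surgery v embolization | Power at 0.05 | Power at 0.01 | Missed at 0.01 |
|---|---|---|---|
| 5% v 10% | 38% | 17% | 83% |
| 10% v 15% | 25% | 10% | 90% |
| 10% v 20% | 67% | 43% | 57% |
| 15% v 25% | 57% | 33% | 67% |
| 15% v 30% | 87% | 70% | 30% |
| 20% v 40% | 96% | 88% | 12% |

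The 0.01 rule costs about 21 points of power at 5% v 10% (38 − 17), 24 at 10% v 20% (67 − 43), 17 at 15% v 30% (87 − 70) and 8 at 20% v 40% (96 − 88). The rest of each miss rate comes from the sample size.

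**3. A result on which the rule and the interval disagree.** Take 14/144 (9.7%) v 29/144 (20.1%). Expected counts per arm are 21.5 with and 122.5 without an event.

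- Test: G = 2[14 ln(14/21.5) + 29 ln(29/21.5) + 130 ln(130/122.5) + 115 ln(115/122.5)] = 6.26, p = 0.012. This is below 6.635, so not significant at 0.01.
- Odds ratio: (29 × 130)/(14 × 115) = 2.34. SE of the log = √(1/14 + 1/29 + 1/130 + 1/115) = 0.350. 95% CI = exp(0.851 ± 1.96 × 0.350) = 1.18 to 4.65, which excludes 1.
- Risk difference: 20.1% − 9.7% = 10.4 points, 95% CI 2.3 to 18.6.

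An exact doubling stays non-significant at 0.01 up to 16 v 32 events (p = 0.0108). It first becomes significant at 17 v 34 (p = 0.008).

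**4. Precision if the arms are equal.** At 10% in both arms the 95% half-width of the risk difference is 1.96 × √(2 × 0.10 × 0.90/144) = 0.069, about 7 points.

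**The case against.** Several stronger readings are tempting, and the document does not support them.

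- **That safety rests on a p-value alone, with no upper bound.** The complication model is the primary outcome's model, so an odds ratio with a 95% interval is planned and an upper limit will be visible. What is absent is a stated way to read it, and a 0.01 label that can contradict it.
- **That comparable complication rates are part of the hypothesis.** They appear in a separate Discussion sentence about what could change practice. Only safety is in the hypothesis sentence, and the formal hypothesis and primary objective cover reoperation alone. Nothing commits the trial to show non-inferiority.
- **That a doubling would usually be missed.** This depends on an unstated rate. By a normal approximation, power for a doubling at 0.01 passes 50% at a control rate of about 11.5% and 80% at about 18%. The adverse event definition is broad, so a high overall rate is possible.
- **That the 0.01 rule is the main cause.** Miss rates are already substantial at 0.05 in most scenarios, because of sample size.
- **That no stronger safety rule exists.** The article refers to a DSMB charter and to section numbers it does not contain, so the primary safety endpoint may be defined elsewhere. Continuous DSMB review, adjudication of serious events and the interim analysis after 100 patients also bear on safety, although none sets a rule for the final safety conclusion.

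A margin or a rule of interpretation could also properly sit in an analysis plan that is not shown, so its absence is not held against the article. What remains is the threshold that the article does state. It covers complications without exception and works in the wrong direction for harm.

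**Conclusion.** The point holds in limited form. The protocol applies a benefit-oriented multiplicity correction to its harm outcome while stating a hypothesis that includes safety. At 144 per arm this lowers power to declare a doubling of complications from 38% to 17% at a 5% control rate, from 67% to 43% at 10%, and from 87% to 70% at 15%. At 20% the loss is small and power stays at 88%. It can also label as not significant a result whose planned 95% interval excludes no difference.

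A reader might infer that the protocol treats p above 0.01 as evidence of safety. It never says so. The supported conclusion is that, at this sample size, a non-significant complication test cannot carry the words safe or comparable at either threshold when rates are low to moderate.

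The figures rest on assumed complication rates, an unadjusted comparison and full follow-up of 144 per arm. The primary analysis is not affected. The reference to a primary safety endpoint does not fit the rest of the article, which has one primary outcome (reoperation) and lists safety as secondary.

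**What to change.** - **Adjustment of significance levels and confidence intervals:** exempt outcome V (adverse and serious adverse events) from the p<0.01 rule.
- **Secondary variable analyses:** beside the planned odds ratio, report the between-arm risk difference in complications and in serious adverse events, each with a two-sided 95% confidence interval.
- **Same section:** state that a non-significant difference will not be read as safe or comparable, and that the conclusion will give the largest excess with embolization that the 95% interval does not exclude.
- **Data Safety Monitoring Board:** reconcile the primary safety endpoint with the outcome list and the single primary outcome. The sponsor should say what was meant; the article does not settle it.

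A margin is optional. If one is wanted, it should be fixed before comparative data are seen and with its feasibility in mind. With equal true rates of 5%, 10% or 15%, one-sided 0.025 and 80% power, a 10-point margin needs 75, 142 or 201 per arm, and a 5-point margin needs 299, 566 or 801. These margins are illustrations.

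Without a margin the change costs wording only, with no added patients or data. The price is that harm differences are reported without multiplicity control and the safety statement is less favourable: with 10% in both arms, an excess of up to about 7 points could not be excluded.

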#### Methods in analysis to handle protocol non-adherence and any statistical methods to handle missing data {20c}

Deviations from the protocol will be assessed continuously and a per-protocol sensitivity analysis will be used to assess the potential impact of such deviations. Characteristics of participants that withdraw their informed consent will be examined to assure that exclusion of such patients will not introduce bias in the analyses. Due to the nature of the trial, missing data on key covariates is unlikely to occur. However, in the event of missing participant data on any variable included in the statistical analysis plan, both complete case analysis and multiple imputation will be performed.

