#### Criteria for discontinuing or modifying allocated interventions {11b}

Post recruitment violation of inclusion and/or exclusion criteria are grounds for termination from the study. Unfavorable vascular anatomy are grounds for crossing over. Dropouts or crossovers will receive standard treatment as indicated by their clinical status and their data is retained unless explicitly denied.

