#### Sample size {14}

The study will include at least 288 patients (control + intervention), with 144 patients per arm. The required total sample size was estimated based on the expected proportion of re-operations (primary outcome) within the control and intervention arms using a two-sided likelihood ratio test with alpha = 0.05 (type I error), beta = 0.2 (type II error), and power of 80% (1-beta). The null hypothesis for this study is that there is no difference between embolization versus surgery for cSDH. The alternative hypothesis was conservatively pre-specified as a different proportion of re-operations between the groups (i.e., a two-sided test was used for power calculation). The expected proportion in the control arm was defined as 17%. This number was based on the average excess operations per patient operated for cSDH in South of Sweden (Skåne) during the last 5 years (2016–2020), as well as a report from the Skåne University Hospital [17]. The expected proportion in the intervention arm was set to 6.5% based on previous reporting evaluating the safety and efficacy of embolization of cSDH as sole treatment [13].

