### Data collection and management

#### Plans for assessment and collection of outcomes {18a}

##### Primary outcome

The diagnosis of cSDH will be made on current imaging and clinical status of the included subject at the time of admittance to the recruiting neurosurgery department. Relevant clinical, radiological, and procedural data will be manually transferred from the participant medical records to the electronic case report form (eCRF). Data on reoperation (Swedish National Board of Health and Welfare Statistics Database) and date of death and primary cause of death (National Cause of Death Registry) will be collected at 3 months and 1 year post procedure. This data will be transferred to the eCRF. Participant medical records will be used to double-check the validity of the register data.

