#### Plans to promote participant retention and complete follow-up {18b}

The study participants are recommended to follow the study protocol. Included participants refusing allocated treatment and crossovers will remain in the study and be included in the intention-to-treat analysis. Additional participants may be enrolled to allow the study to meet its designed sample size dimensions to allow for a sufficiently powered per-protocol-analysis.

Participation in this investigation is voluntary, and the subject may withdraw at any time. All enrolled subjects will be included in data analysis unless they withdraw permission for their data to be used. The sponsor will retain and continue to use any data collected prior to the withdrawal of consent, unless specified by the subject.

In the event the subject chooses to withdraw, he/she will be instructed to contact the Investigator immediately. Withdrawal from the investigation will not affect the subject's standard of care. The subject will be informed of any significant information regarding new findings that may develop during the course of the study that may relate to his or her willingness to continue participation as a study subject.

Subjects will participate in their routine follow-up and allow this data to be gathered. If their participation is terminated, any of their data which has been already gathered will continue to be included. The completion of a subject’s participation in the study or early departure from the study must be fully documented in the subject’s medical records. Subjects will be considered discontinued from the study if any of the following occur:Subject voluntarily withdraws from the study: A subject may withdraw consent from study participation at any time. The subject will be offered to give a reason for their withdrawal. If voluntarily given, this reason will be recorded in the eCRF.Subject withdrawn from the study by the investigator: An investigator may withdraw an enrolled subject from the study for the following reason:

If participation in the study is life threatening for the subject or at the investigators own discretion.

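### The missing-data section speaks of excluding participants who withdraw consent while the retention section analyses them unless they refuse data use, and comparing characteristics cannot assure that exclusion is unbiased

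*Protocol article*

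**What the plan says.** Four sections of the protocol article bear on participants who withdraw.

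- **Section {20c}** (non-adherence and missing data): "Characteristics of participants that withdraw their informed consent will be examined to assure that exclusion of such patients will not introduce bias in the analyses". For missing values it adds that "both complete case analysis and multiple imputation will be performed".
- **Section {18b}** (retention and follow-up): "All enrolled subjects will be included in data analysis unless they withdraw permission for their data to be used", and "The sponsor will retain and continue to use any data collected prior to the withdrawal of consent, unless specified by the subject". A later sentence carries no exception: "If their participation is terminated, any of their data which has been already gathered will continue to be included".
- **Section {11b}** (discontinuing or modifying interventions) says of dropouts and crossovers that "their data is retained unless explicitly denied".
- **Section {11c}** (adherence) keeps those who refuse their allocated treatment, and crossovers, in the intention-to-treat analysis with a similar exception.

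Treatment allocation is open (section {17a}). Reoperation and death are taken from national registers, and medical records are used to check the register data (section {18a}).

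**The concern.** Sections {20c} and {18b} both start from withdrawal of consent. In {20c} the consequence named is exclusion. In {18b} it is continued use of what was already collected, with exclusion only if the participant also refuses data use. A patient who withdraws without that refusal therefore belongs to the primary analysis set under one section and not under the other.

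The safeguard in {20c} raises a second question. It looks at the characteristics of those who leave in order to assure that their removal causes no bias. Exclusion after randomisation biases the comparison when leaving is related to outcome differently in the two arms. In an open trial, leaving may follow from the allocation or from the clinical course, and similar baseline characteristics do not rule that out. The primary outcome has few events: at the planned rates about 0.17 × 144 = 24 in the control arm and 0.065 × 144 = 9 in the embolization arm. A handful of excluded events can therefore matter.

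**Working it through.** **1. The plan's own figure.** Section {14}: "The study will include at least 288 patients (control + intervention), with 144 patients per arm". The inputs are 17% v 6.5%, a two-sided likelihood ratio test, alpha 0.05 and 80% power. Per pair of patients the noncentrality is 2 × [KL(0.17, 0.1175) + KL(0.065, 0.1175)], where KL(p, q) = p ln(p/q) + (1 − p) ln((1 − p)/(1 − q)). This is 2 × (0.01188 + 0.01555) = 0.05487. For 80% power on 1 df the requirement is 143.06, so 144 per arm. At 144 the noncentrality is 7.90 and power is 80.3%. The figure reproduces, and this point does not alter it.

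**2. The rules side by side.** Take a patient reoperated on day 20 who withdraws on day 40.

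| Patient's choice | {18b} | {20c}, literal | {20c}, refusals only |
|---|---|---|---|
| Withdraws, does not refuse data use | Analysed, event | Excluded | Analysed, event |
| Withdraws and refuses data use | Removed | Excluded | Removed |

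The literal reading differs from {18b} in the first row. The narrower reading agrees in both rows, but then the check concerns only people who have refused use of their data, and their characteristics may not be available for it.

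**3. How much the check can show.** The article names no test and no withdrawal rate, so these are illustrations at assumed rates.

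- A difference of 0.5 SD between withdrawers (k) and the rest of the 288: power = Φ(0.5/√(1/k + 1/(288 − k)) − 1.96).
  - 2% (k = 5.76): SE 0.421, power 22%.
  - 5% (k = 14.4): SE 0.270, power 46%.
  - 10% (k = 28.8): SE 0.196, power 72%.
- A binary characteristic at 5% withdrawal, Fisher's exact test, 60% v 40% and 70% v 40%: one arm (7 v 137) 16% and 32%; both arms pooled (14 v 274) 28% and 56%.

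**4. Bias in the primary comparison.** Assume a true risk of 17% in both arms, with a fraction w excluded from one arm only and a reoperation risk r among those excluded. The observed risk in that arm is (0.17 − w·r)/(1 − w). The last column is the two-sided rejection rate of a pooled normal test with 144 and 144(1 − w) patients.

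| w | r | Observed risk | Rejection of a true null |
|---|---|---|---|
| any | 17% | 17.0% | 5.0% |
| 2% | 50% | (0.17 − 0.010)/0.98 = 16.3% | 5.3% |
| 5% | 34% | (0.17 − 0.017)/0.95 = 16.1% | 5.5% |
| 5% | 50% | (0.17 − 0.025)/0.95 = 15.3% | 6.8% |
| 10% | 34% | (0.17 − 0.034)/0.90 = 15.1% | 7.0% |
| 10% | 50% | (0.17 − 0.050)/0.90 = 13.3% | 13.3% |

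**5. A borderline result.** z = (difference in proportions)/√(p̄(1 − p̄)(1/n₁ + 1/n₂)), unadjusted.

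- All randomised, 14/144 (9.7%) v 24/144 (16.7%): p̄ = 38/288 = 0.132, SE 0.0399, z = 1.74, p = 0.08.
- After excluding 7 per arm (about 5%), with two events among the excluded embolization patients and none among the excluded controls, 12/137 (8.8%) v 24/137 (17.5%): p̄ = 36/274 = 0.131, SE 0.0408, z = 2.15, p = 0.03.
- The likelihood ratio test gives 0.080 and 0.031.
- If one of the excluded controls also had an event (12/137 v 23/137), p = 0.047; with two (12/137 v 22/137), p = 0.07.

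**The case against.** The strongest reply is that the protocol has one rule. Sections {11b}, {11c} and {18b} all make retention the default and remove only those who refuse. Section {20c} does not say that everyone who withdraws consent is excluded, and read with the others it can mean only those whose data have to be dropped. This stands as a possible reading. A reader might infer an outright contradiction, or that {18b} keeps such data unconditionally. The text does not support either: two sentences of {18b} allow refusal, and the harmonised reading is available. What remains is that {20c} does not say so, and the harmonised reading leaves the check possibly short of data.

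A second reply is that comparing withdrawers with the rest is an ordinary descriptive step, that no significance test is named, and that multiple imputation is planned. The step can indeed reveal a measured imbalance, so it would be wrong to infer that it is useless. But it does not address withdrawal driven by allocation or course, and the article states no consequence if a difference appears. Imputation is provided for missing values and is not said to restore patients who were excluded.

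A third reply concerns size. No withdrawal rate is given, and at 2% the distortion is slight. It is also tempting to illustrate the danger with 6 of 7 excluded embolization patients having been reoperated. From an arm with 12/144 events, random withdrawal would give 6 or more with a chance of about 6 in 10 million, and that comparison is significant with or without the exclusions (p = 0.03 and 0.0005). It shows nothing useful. The Discussion does describe slower improvement after embolization, but it does not link this to withdrawal, so arm-related withdrawal is plausible and not documented.

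**Conclusion.** The point holds in a limited form. Read literally, {20c} and {18b} give different primary analysis sets for a patient who withdraws without refusing data use. Read narrowly they agree, and the check may then depend on data that were denied. On both readings the comparison of characteristics cannot deliver the assurance that {20c} attaches to it.

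The size is conditional. It rests on an assumed withdrawal rate and on withdrawers differing in reoperation risk by arm; if their risk equals that of the rest, there is no bias. With up to 2% excluded from one arm at a 50% risk, the false-positive rate is at most 5.3%. At 5% and 10% it is 6.8% and 13.3%. The borderline example shows that two excluded events can move p from 0.08 to 0.03 when no control event is lost; it is a scenario, not a forecast. The planned sample size is unaffected. This should be corrected, but it does not undermine the design.

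**What to change.** Reword {20c} to match {18b}: all randomised participants are analysed as randomised with data up to withdrawal; only those who explicitly refuse use of their data are removed; and the number removed is reported by arm. The sentence in {18b} that carries no exception should take the same one.

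Replace the check that is meant to assure absence of bias with a sensitivity analysis of the primary outcome. It should vary the assumed reoperation outcome of removed or unobserved patients separately by arm, as best and worst case or as a tipping point. For patients who refused data use it needs only their number by arm. A description of withdrawers whose data may be used can stay as description.

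The cost is a wording change and one extra analysis. The register and record sources for reoperation are already in the plan.
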